### Outcomes

While expert opinion and cohort studies are readily available, the question of which of two commonly performed operations provide the best treatment for GORD in the obese population will not be settled until a RCT is performed. GORD is one of the most common medical conditions afflicting the Western population, and rates of obesity continue to increase and will remain a problem for generations to come. As such, the number of patients to whom the trial findings can be applied in the future are very large. Analysis of local data confirms that the number of patients seeking surgical treatment for GORD in our health district is slowly increasing, as is their BMI. In addition, fundamental questions regarding oesophagogastric pathophysiology in obese patients with GORD are unanswered currently. This is in large part due to a piecemeal approach in the literature to date. Similarly, there has never been a randomized trial of two surgical procedures of similar magnitude where only one is expected to induce weight loss; this brings a unique opportunity to study gut neurohormonal changes after a bypass operation. Insights gained by the formal, in-depth study of pre- and postoperative physiological parameters will greatly add to the basic understanding of this patient population and undoubtedly lead to further advances in the field.

For participants in both control and treatment groups, outcomes will be measured at baseline, 1 year and 5 years after surgery. The primary outcome is GORD symptom scores (assessed with the GERD-HRQL survey). Secondary outcome(s) are GORD symptom scores (assessed with the GERD-HRQL survey) at 5 years, the percentage of total time spent with pH < 4 in the oesophagus, the presence and severity of oesophagitis, and patient-reported outcomes. Gastrointestinal-specific quality of life will be assessed using the SAGIS questionnaire^42^ (including dysphagia, belching, bloating, flatulence, and altered bowel habit), while overall quality of life will be assessed using SF-6Dv2^43,44^. The operative metrics and surgical morbidity measures will be operating time (measured in minutes), pain score (measured using a visual analogue score and oral morphine equivalents), length of hospital stay (measured in days), the Comprehensive Complication Index^61^, the development of complicated gallstone disease, and readmission rate (at 90 days). Bodyweight changes will be monitored. With respect to the changes in pathophysiological parameters contributing to GORD, the transient lower oesophageal sphincter relaxation episodes and duration on high-resolution manometry and bladder pressure measurement (as a surrogate for intra-abdominal pressure) will be measured both before and after surgery.

For randomization, an adaptive procedure will be used to stratify patients according to sex, BMI (class I or uncomplicated class II), and percentage of time with oesophageal pH < 4 (4–10 per cent and more than 10 per cent), with the use of a ‘biased coin’ procedure to balance treatment assignments^60^. The symmetric Kullback–Leibler divergence minimization method, which allows the use of both continuous and categorical factors will be used^62^. A 1:1 assignment will be used with a block size of six. The goal is that the patient will be kept blinded until after the operation. To achieve this, group allocation will be performed by a database manager (non-clinician) the morning before surgery (to facilitate operating room scheduling and equipment preparation). It will be directly communicated to the operating surgeon.

For blinding, the allocation sequence will be concealed from researchers responsible for assigning participants. The patient will be kept blinded until after the operation. Where possible, data analysis will be conducted in a blinded fashion.

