**Conclusion:**

This trial will determine whether LRYGB is effective and acceptable as an alternative to LF for the surgical treatment of GORD in obese patients

**Registration number:** Australian New Zealand Clinical Trials Registry (ANZCTR): ACTRN12622000636752p (https://www.anzctr.org.au/).

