For a patient with a normal BMI and an established diagnosis of GORD who has met the indications for surgery, the standard procedure is LF^24^. For a patient with complicated class 2 or class 3 obesity who also meets the surgical criteria for GORD, the priority is arguably weight loss rather than GORD. From an overall health perspective, the evidence suggests they are better served by bariatric surgery, which brings, among other benefits, an increased life expectancy^11^. Therefore, LRYGB would usually be the procedure of choice because unlike other bariatric procedures, it could achieve the dual benefits of weight loss and improvement in GORD^25,26^.

However, in patients with class 1 or uncomplicated class 2 obesity wanting surgery for GORD, there is clinical equipoise. There is conflicting evidence regarding the outcomes of LF in obese patients^26^. Many cohort series show that when compared with non-obese patients, LF is as safe and effective at improving GORD in obese patients^27–29^. Yet some series have showed reduced control of GORD and greater technical difficulty (measured as longer operating times, more complications, and longer duration of stay)^25,30^. Recurrence of GORD seems to be a particular problem in obese patients in the long term (more than 10 years), with more than 25 per cent having troublesome symptoms and objective evidence of GORD^31,32^. In addition, LF is not generally thought to achieve significant weight loss or improvement in obesity-related complications, which is important to appreciate, because the natural history of patients with class I or uncomplicated class II obesity is likely progression to a higher class^33^.

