### Preoperative work-up

All patients will complete symptom and quality-of-life assessments for GORD health-related quality of life (GERD-HRQL)^41^, gastrointestinal health (structured assessment of gastrointestinal symptoms scale; SAGIS)^42^ and overall health (Short-Form Six-Dimension version 2; SF-6Dv2)^43,44^. All patients will undergo global health screening and optimization of medical co-morbidities. There will be a focus on obesity-related conditions (for example, type 2 diabetes mellitus (fasting blood sugar level and glycated haemoglobin (HbA1c)), cardiovascular disease (cardiac risk assessment, 12-lead ECG ± echocardiogram ± exercise stress testing), non-alcoholic fatty liver disease (liver function tests ± abdominal ultrasound), obstructive sleep apnoea (STOP-BANG questionnaire ± sleep physician review),^45^ and nutrition (clinical assessment and protocolized blood tests)), with operating risk scoring conducted with the Elixhauser score^46,47^.

All patients will undergo blood tests to assess nutritional and hormonal parameters, oesophago-gastro-duodenoscopy (OGD) with oesophageal biopsy, 24-h pH and impedance study, solid-state high-resolution oesophageal manometry (reporting using the Chicago IV classification), breath tests (gastric emptying and small intestinal bacterial overgrowth), and bladder pressure measurements. To minimize patient discomfort and achieve the most reliable results, the bladder pressure measurement will be performed at the time of OGD while under sedation. The ambulatory pH probe will be placed at the conclusion of the OGD, again under sedation to minimize discomfort.

In keeping with enhanced recovery after surgery (ERAS) principles^48^, both patient groups will receive operation-specific preoperative counselling about their procedure and recovery interval including expectation setting regarding usual milestones of recovery. All patients will receive counselling and printed literature (pre-existing through Metro South Dietetics service) on how to implement a very-low-calorie diet for 2 weeks before surgery, which can achieve up to 80 per cent reduction in hepatic steatosis^49^.

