### Postoperative care

Postoperative recovery and discharge will be in keeping with standard clinical practice. This includes multimodal analgesia with intra- and postoperative opiate minimization, early mobilization with physiotherapy input, graduated compression stockings, and low molecular weight heparin using local evidence-based guidelines, immediate cessation of anti-acid medication^55^, and no routine postoperative imaging. The target in-hospital stay is 1 night^56^. Once recovered from the anaesthetic, all patients will commence a clear liquid diet (low calorie, low sugar, non-carbonated, caffeine-free, and alcohol-free)^57^. Progression to full liquids (high protein, low calorie, and low sugar) will occur on day one after surgery with slow introduction of pureed or mashed food over the following weeks at the discretion of the operating surgeon.

At 1, 3, 6, 12, 24, 36, 48, and 60 months after surgery, all patients will repeat the quality-of-life assessments, be weighed, and have blood tests to assess nutritional and hormonal parameters. At 1 and 5 years, all patients will undergo repeat global health assessment, OGD with oesophageal biopsy, 24-h pH + MII study, oesophageal manometry, breath tests (gastric emptying and small intestinal bacterial overgrowth), and bladder pressure measurements. In keeping with published Australian recommendations^58^, and guided by some of the blood test results from above, LRYGB patients will receive ongoing long-term dietitian review and nutritional supplementation.

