### Objectives

The primary objective is to determine if there is a difference in treatment success (defined as a reduction of 50 per cent of more in the GERD-HRQL score between the preoperative value and the 1-year value) following LRYGB compared with LF (as used in two contemporary high-impact GORD treatment RCTs^59,60^).

With this respect, the trial was design according to the following hypotheses:

*H_0_*: Postoperative GORD symptom scores (GERD-HRQL) will be similar for patients undergoing LRYGB *versus* LF for GORD at 1 year.
*H_A_*: Postoperative GORD symptom scores (GERD-HRQL) will be different for patients undergoing LRYGB *versus* LF at 1 year.

The secondary objectives are to determine any differences in terms of:

Treatment success at 5 years (decrease of 50 per cent of more in the GERD-HRQL score between the preoperative value and the 5-year value)Objective measures of GORD at 1 and 5 yearsNon-GORD gastrointestinal symptom scores at 1 and 5 yearsOverall health at 1 and 5 years

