### Statistical considerations

There are limited data to guide the sample size calculation. A pilot phase of 20 patients (10 in each arm)^63^ will be completed at the Upper Gastrointestinal Surgery Unit, Princess Alexandra Hospital. This will allow an assessment of recruitment rate and an analysis of the primary outcome to enable the power calculations and trial duration to be recalculated and ensure that the trial remains practical and can be completed. In addition, any initial logistical issues can be resolved. Thereafter, the trial will be extended across Logan Hospital, QEII Jubilee Hospital and the Royal Brisbane and Women’s Hospital.

The trial will be powered based on the primary outcome alone. Using *α* = 0.05, *β* = 0.8, a randomization ratio of 1: 1 and a mean(s.d.) GERD-HRQL score of 8(8) after LF in class I and II obesity^64^ and 5 after LRYGB^65^, a sample size of 164 would be required. Assuming a 10 per cent dropout, there would need to be 91 patients in each arm. This equates to approximately 2 years of referrals of eligible patients to the Princess Alexandra Hospital alone. Assuming participation of the other hospitals and 50 per cent uptake, a conservative estimate is that recruitment will take approximately 3 years.

Acknowledging the lack of data to guide power calculations and hence the possibility that the alternative treatment (LRYGB) may give the same mean GERD-HRQL score as the control treatment (LF), a planned non-inferiority analysis will also be performed. Using *α* = 0.05, *β* = 0.9, a randomization ratio of 1: 1, a mean(s.d.) GERD-HRQL score of 8(8) after LF in class I and II obesity and a non-inferiority limit (d) of 4, a sample size of 138 is required. Assuming a 10 per cent dropout, there would need to be 77 patients in each arm.

Given that both superiority and non-inferiority analyses are planned, it is appropriate to perform both intention-to-treat and per-protocol analyses. Continuous data will be tested using a Student’s *t* test if data are normally distributed or otherwise a Mann–Whitney *U* test. Normality of continuous data will be assessed with the Shapiro–Wilks test. Categorical data will generally be assessed using the chi-squared test or Fisher’s exact test when the assumptions of the chi-squared test are not met. All *P* values will be two-tailed (except for non-inferiority analysis), and significance will be set at 0.050.

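### The 5-year symptom outcome rests on the 60-month GERD-HRQL value alone, although annual scores from 12 to 48 months are collected and could inform patients missing at 60 months

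*Protocol article*

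**What the plan says.** Under Preoperative work-up, "All patients will complete symptom and quality-of-life assessments for GORD health-related quality of life (GERD-HRQL") is listed with the gastrointestinal and overall-health questionnaires. Postoperative care repeats that set: "At 1, 3, 6, 12, 24, 36, 48, and 60 months after surgery, all patients will repeat the quality-of-life assessments". GERD-HRQL is therefore scheduled at five annual visits, from 12 to 60 months, as well as at 1, 3 and 6 months.

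The sections that define outcomes are narrower. Outcomes says that "outcomes will be measured at baseline, 1 year and 5 years after surgery". The late symptom result appears in two forms:

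- In Objectives, as a responder status: "Treatment success at 5 years (decrease of 50 per cent of more in the GERD-HRQL score" from the preoperative value).
- In Outcomes, as a score: "GORD symptom scores (assessed with the GERD-HRQL survey) at 5 years".

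Statistical considerations says "The trial will be powered based on the primary outcome alone". For continuous data it names the t test or Mann–Whitney test, and for categorical data the chi-squared or Fisher test. No objective, outcome or analysis sentence gives a role to the 24, 36 or 48-month scores.

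**The concern.** The 5-year comparison addresses whether symptom control lasts. It is also the comparison most exposed to loss to follow-up. The plan's 10% dropout allowance is not tied to year 5.

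A two-group test on the 60-month value uses only patients seen at 60 months. Someone followed to month 48 and then lost drops out of the comparison, although four annual scores are on file. Two things are at stake:

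- **Precision.** Information already collected on the missing patients is unused.
- **Bias.** A completers-only comparison is sound only if, within each arm, being missing at 60 months is unrelated to the score. A model that includes the earlier scores allows missingness to depend on how the patient was doing at those visits, which is a weaker and more plausible condition.

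The time points in Outcomes also do not match the schedule in Postoperative care, so a reader cannot tell what the interim scores are for.

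**Working it through.** The plan gives no figure on this point, so there is none to reproduce. The check sets the schedule against the outcome definitions and then sizes what the earlier scores could add.

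**1. Schedule against use**

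| GERD-HRQL visit | Scheduled | Named in an objective or outcome |
|---|---|---|
| 12 months | yes | yes (primary) |
| 24, 36, 48 months | yes | no |
| 60 months | yes | yes (secondary) |

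**2. Patients affected**

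From the document: 91 patients per arm, 182 in total. Assumed, because the document does not give it: 20% to 30% missing at 60 months.

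- 182 × 0.20 = 36
- 182 × 0.30 = 55

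So 36 to 55 patients would be absent from the stated 5-year comparison. How many of them would have scores to month 48 is unknown. The next step takes the best case, in which all do.

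**3. Gain in precision for the 60-month contrast**

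Assumed: the same correlation r between any two annual scores, with r from 0.5 to 0.7. The four earlier scores (12, 24, 36 and 48 months) then explain this share of the variance of the 60-month score:

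R² = 4r² / (1 + 3r)

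- r = 0.5: 1.00 / 2.5 = 0.40
- r = 0.7: 1.96 / 3.1 = 0.632

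Let f be the fraction missing at 60 months. Per unit σ²/n, completers only give a variance of 1/(1 − f). The model gives (1 − R²)/(1 − f) + R². The ratio of model to completers is therefore 1 − f·R².

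| f | r = 0.5 | r = 0.7 |
|---|---|---|
| 0.20 | 1 − 0.20 × 0.40 = 0.92 | 1 − 0.20 × 0.632 = 0.87 |
| 0.30 | 1 − 0.30 × 0.40 = 0.88 | 1 − 0.30 × 0.632 = 0.81 |

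The variance is 8% to 19% lower. The standard error is multiplied by √0.92 = 0.96 to √0.81 = 0.90, so it is 4% to 10% smaller. With nobody missing, f = 0 and the earlier scores add nothing to this contrast.

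**4. Why not the average over years 1 to 5**

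The mean of five equally correlated visits has (1 + 4r)/5 of the variance of one visit. That is 0.60 at r = 0.5 and 0.76 at r = 0.7, so standard-error factors of 0.775 and 0.872. The gain looks larger (13% to 23%), but it helps only if the treatment difference is constant. Suppose instead that the difference grows linearly from 0 at year 1 to D at year 5. The five differences are 0, 0.25D, 0.5D, 0.75D and D, with mean 0.5D. Relative to the 60-month comparison, the signal-to-noise ratio is then:

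- r = 0.5: 0.5 / 0.775 = 0.65
- r = 0.7: 0.5 / 0.872 = 0.57

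That is a loss of 35% to 43% in the very situation where durability matters.

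**The case against.** **The choice of analysis may be left to a fuller document.** Handling of missing secondary data and the choice of a longitudinal model are commonly left to the full protocol or analysis plan, which are not shown. This stands in part. A reader might infer that the interim scores are excluded or ignored, but no sentence says so. The list of time points in Outcomes cannot be exhaustive, since the same section includes operating time and 90-day readmission. What remains is that the article does fix the late symptom outcome at 5 years and does name its tests, and as stated these use only the 60-month value.

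**A fixed 5-year comparison is a legitimate secondary endpoint.** It is, and the point does not ask to replace it. The model estimates the same 60-month contrast. Nor does durability rest on symptoms alone, because oesophageal acid exposure and oesophagitis are also assessed at 5 years.

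**The Introduction does not make the interim visits essential.** A reader might infer that the protocol describes gradual recurrence after LF within follow-up. The text does not support that: "Recurrence of GORD seems to be a particular problem in obese patients in the long term (more than 10 years") gives a horizon beyond every scheduled visit and no trajectory. The 60-month visit is the closest to it.

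**The abstract's conclusion does not overreach.** A reader might also take "This trial will determine whether LRYGB is effective and acceptable as an alternative to LF" as a claim resting on the 1-year result. The sentence states the trial's purpose without tying it to one time point, and the trial has 5-year objectives.

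**Conclusion.** The point holds as a modest improvement to a secondary objective. Annual GERD-HRQL scores are scheduled, but the 5-year symptom outcome as stated does not use the interim scores of patients missing at 60 months.

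Using them would lower the variance of the 60-month contrast by about 8% to 19%. That figure assumes 20% to 30% loss by year 5, equal correlations of 0.5 to 0.7, and earlier scores on file for everyone lost, so it is a best case. It is derived for the continuous score and does not carry over directly to the responder status. The weaker missing-data assumption is the other benefit, and it does not depend on these figures.

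The sample size, the 1-year primary comparison and the validity of a 5-year endpoint are unaffected.

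**What to change.** In Outcomes and Statistical considerations:

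1. Estimate the 5-year GERD-HRQL difference as the 60-month contrast from one repeated-measures model on all scheduled scores from 12 to 60 months, with the baseline score as a covariate.
2. Where the 5-year responder status is missing, handle it with the same earlier scores, for example by multiple imputation of the 60-month score before it is classified.
3. Report the proportion with at least a 50% reduction at each annual visit, labelled descriptive.
4. Do not use the average over years 1 to 5 as the durability measure.
5. Reconcile the time points in Outcomes with the schedule in Postoperative care, and say what the interim scores are for.

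If a fuller document already specifies this, only item 5 and a cross-reference are needed. The cost is some wording and a little more analysis work, with no added visits or questionnaires. The change should be made before outcome data are seen, so that the choice of visits and model is not post hoc.

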### Interventions

Patients will be randomized to either LF or LRYGB, with LF being designated as the ‘control’ procedure. Both operations are widely used in contemporary practice.

For LF, the patient will be supine or placed in lithotomy position. Four laparoscopic ports and an epigastric retractor will be placed. A dissection of the oesophageal hiatus will be performed, preserving both vagus nerves, and a cruroplasty will be performed as required using non-absorbable sutures. Sufficient fundal mobility will be achieved to allow a partial fundoplication (anterior 180 degree or posterior 270 degree) and fixation of the fundus to the diaphragmatic crura and oesophagus will be achieved with non-absorbable sutures. In the absence of evidence showing major differences in long-term GORD symptom control or dysphagia for these two styles of fundoplication, the wrap type as well as division of the superior short gastric vessels and use of a calibrating device will be at the discretion of the operating surgeon^50^. Crural dissection, cruroplasty, and fixation of the distal oesophagus and fundus will be performed as necessary. Operating technique will be recorded to allow possible future analyses.

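### Hospital is not a balancing factor in the minimisation of a four-hospital trial, so chance imbalance by site is likely; the cost is a modest loss of precision and comparability, not bias

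*Protocol article*

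**What the plan says.** The randomisation text stands in the protocol article under Outcomes. It names three balancing factors. The first two are given thus: "an adaptive procedure will be used to stratify patients according to sex, BMI (class I or uncomplicated class II"). The third is acid exposure in two bands: "percentage of time with oesophageal pH < 4 (4–10 per cent and more than 10 per cent"). On the method it states: "The symmetric Kullback–Leibler divergence minimization method, which allows the use of both continuous and categorical factors will be used". It adds: "A 1:1 assignment will be used with a block size of six". Blocks are not said to run within hospital. A non-clinician database manager allocates on the morning before surgery and tells the operating surgeon.

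Under Statistical considerations, the trial begins at a single hospital: "A pilot phase of 20 patients (10 in each arm"). Then: "Thereafter, the trial will be extended across Logan Hospital, QEII Jubilee Hospital and the Royal Brisbane and Women’s Hospital". Continuous outcomes are compared with a t test or Mann–Whitney test and categorical ones with a chi-squared or Fisher test. No site term is mentioned.

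Under Interventions, several technical choices are left open. For fundoplication, these rest with whoever operates: "the wrap type as well as division of the superior short gastric vessels and use of a calibrating device will be at the discretion". For bypass, the anastomotic technique is the surgeon's choice and the alimentary limb varies within a stated range. Under Ethical considerations, all surgeons are said to be credentialled in both operations.

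**The concern.** The factor list is explicit, so the absence of hospital is a stated choice and not a detail deferred to another document. In a surgical trial at four hospitals, local practice can plausibly affect recovery, length of stay, operating time and complications, all of which are listed as outcomes. If the arms are uneven within a hospital, part of any difference between hospitals enters the comparison of the two operations. The hospitals with few patients are the most exposed. Because the stated tests are unadjusted, nothing described in the article would remove that component afterwards. Balance at allocation can be secured only before patients are randomised.

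**Working it through.** The article gives no figure for this point, so there is none to reproduce. It also gives no hospital sizes and no between-hospital differences; those below are assumptions.

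**Inputs from the article.** 91 patients per arm (182 in total) after dropout; 164 analysed, or 82 per arm; GERD-HRQL s.d. 8 (given for fundoplication, taken here for both arms); planned difference 8 − 5 = 3 points; non-inferiority limit 4 points. Whether 164 follows from the stated assumptions is a separate matter and does not affect this point.

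**Step 1: how often a hospital is unevenly split.** Simulated trials of 182 patients used Pocock–Simon minimisation (standing in for the Kullback–Leibler method), a biased coin of 0.8 and three two-level factors, with and without hospital as a fourth. The block of six was not modelled. Two separate runs were made: one of 4,000 trials per scenario, and one of 1,500 with the 20 pilot patients placed first at one site. The table shows the proportion of trials with at least one hospital split 60:40 or worse.

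| Assumed site shares | Without hospital | With hospital |
|---|---|---|
| 40/20/20/20% | 47% and 45% | 0.4% and 0.5% |
| 55/15/15/15% | 62% and 60% | 4% in both |

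A cruder check ignored all factors and fixed only the overall 91:91 split. It gave 42% for sizes 46/46/45/45, 67% for 92/30/30/30 and 86% for 122/20/20/20. For a split of 65:35 or worse the figures were 8%, 19% and 55%.

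**Step 2: what this does to the primary outcome.** Let one hospital hold n = 0.20 × 182 = 36.4 patients and differ from the rest by D = 4 points. With hospital ignored and 91 per arm overall, the number A of its patients in one arm has variance n × ¼ × (182 − n)/181 = 36.4 × 0.25 × 145.6/181 = 7.32, so s.d. 2.71. The arm difference at that hospital, A − B, has s.d. 2 × 2.71 = 5.41 patients. The shift in the mean difference is D(A − B)/91, with s.d. 4 × 5.41/91 = 0.24 points. The minimisation simulation gave the same 0.24 without hospital, and 0.08 with it.

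**Step 3: compare with the standard error.** SE = 8 × √(2/82) = 1.25 points, variance 1.56. The variance removed is 0.24² − 0.08² = 0.0576 − 0.0064 = 0.051, and 0.051/1.56 is about 3%. The SE would fall to √(1.56 − 0.051) = 1.23.

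**Step 4: the unlucky trial.** In the cruder check, if the first hospital differs from the others by 2 points, the shift stays within about 0.3 points in 95% of trials (9–10% of the planned 3). If it differs by 4 points, the bound is about 0.5–0.6 points (18–21%). With arms level to within 2 patients at each hospital, the shift is at most 2 × 2/91 = 0.04 or 4 × 2/91 = 0.09 points.

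**Step 5: the cost of adding the factor.** The mean worst imbalance on the other factors rises from 2.1 to 2.4–2.5 patients. In a further simulation with coin 0.8, guessing that the next patient goes to the arm under-represented at one's own hospital was right 53% of the time without hospital as a factor and 61% with it.

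**The case against.** The strongest reply is that this is a refinement and that the 60:40 figure describes tidiness more than harm. Much of that stands.

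- **Not bias.** A reader might infer that the comparison is confounded by hospital. The documents do not support that. Patients within each hospital are randomised concurrently, so any imbalance is chance and is already part of the standard error.
- **Not caused by staggered opening.** A later start does not itself create imbalance; small sites are simply more exposed.
- **Not a cure for operator differences.** Wrap type, short gastric division and calibrating device concern fundoplication only; anastomosis and limb length concern bypass only. No balancing by hospital can level a choice that exists in one arm. The number of surgeons per hospital is not given, so hospital only partly stands in for surgeon.
- **Variation is restrained.** Surgeons are credentialled in both operations, and both arms share enhanced-recovery care and a one-night target stay. Nothing in the article shows that site is the main source of variation.
- **The assumed 4-point site effect is generous.** It equals the whole non-inferiority limit.
- **Other documents may help.** Blocks might run within hospital, and an analysis plan not shown might adjust for site. The article says neither, so it cannot be said that nothing holds the arms level within a site; only that nothing stated does.
- **Predictability.** Surgeons are told each allocation and can keep a tally. The rise from 53% to 61% is a real cost. It is limited by the biased coin, the non-clinician allocator and allocation only on the morning before surgery.

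What remains is that the stated list omits hospital, the named method accepts categorical factors, and the omission cannot be repaired after randomisation.

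**Conclusion.** The point holds as a modest matter of precision and comparability. Under the assumed shares, roughly half of such trials would end with at least one hospital split 60:40 or worse, and very few would with hospital as a factor. For GERD-HRQL the gain is about 3% of the variance of the mean difference, even under a generous assumed site effect. A larger gain for operating time or length of stay is plausible, but the documents give nothing with which to quantify it. The omission itself is certain from the text. The size of the consequence rests wholly on assumed site shares and site effects, and on Pocock–Simon minimisation as a stand-in. Low to moderate priority.

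**What to change.** - Add hospital (four levels) as a categorical factor in the Kullback–Leibler minimisation from the opening of the second site, with the pilot patients entered under the first hospital.
- Keep the biased coin, so that allocation within a hospital stays uncertain.
- Include hospital as a term in the analysis. An unadjusted test leaves between-hospital variance in the standard error, so balance at allocation alone would not yield the precision.
- State whether the block of six runs within hospital, and how it fits with the minimisation.

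The cost is one more variable in the allocation program and a few sentences in the protocol, with no extra patients or visits. Balance on sex, BMI class and acid exposure becomes slightly looser, and allocation within a hospital somewhat easier to guess; the protocol should acknowledge both.
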